## Abstract

**Objective::**

Evaluate the feasibility of ERAS-based home exercise pre-rehabilitation in patients awaiting kidney transplantation.

**Methodology::**

The proposed feasibility trial will be a single-arm, single-center study. A total of 47 ESRD patients awaiting kidney transplantation will be selected as subjects to undergo personalized family exercise pre-rehabilitation, including aerobic exercise, functional resistance exercise, and flexibility training. Briefly, a 6-minute walking test (6MWT), 4-meter gait speed, grip strength, and sit-to-stand test will be used as the main outcome indicators. The effect of family exercise pre-rehabilitation on the optimization of body function in ESRD patients undergoing kidney transplantation will be assessed. The days of hospitalization after kidney transplantation, postoperative complications, health survey (the Short Form Health Survey, SF-36), and the Hospital Anxiety and Depression Scale (HADS) will be used as secondary outcome indicators to evaluate the improvement of quality of life, psychological function, and postoperative rehabilitation of patients after kidney transplantation. These indexes will be collected before and after intervention (baseline and before kidney transplantation), before discharge (after kidney transplantation), and 1 month after discharge.

**Conclusion::**

This study will evaluate the effect of ERAS-based home exercise pre-rehabilitation on patients awaiting kidney transplantation, and possibly determine an application protocol for this population.

**Trial registration::**

Chinese Clinical Trial Registry, ChiCTR2000037846. Registered on September 2, 2020.

## Introduction

1

End-stage renal disease (ESRD) refers to the development of chronic kidney disease to the end stage, the glomerular filtration rate is lower than 15 mL/(min 1.73 m^2^), and its treatment methods include hemodialysis, peritoneal dialysis, and kidney transplantation.^[1]^ According to the World Health Organization, the incidence of chronic kidney disease in China is higher than 10.8%, more than 0.03% of which will develop to ESRD,^[2]^ seriously affecting the life expectancy and quality of life of patients. Compared with dialysis treatment, renal transplant recipients have a higher survival rate and quality of life and can obtain better clinical outcomes.^[3]^ Kidney transplantation is the only radical treatment for ESRD. According to statistics, China has completed more than 10,000 kidney transplants in 2017.^[4]^ With the continuous maturity of kidney transplantation technology, optimizing perioperative management, reducing perioperative complications, and promoting rapid recovery of patients have become the focus of the transplantation team in recent years. The concept of surgery has changed from a “disease”-centered biomedical model to a “patient”-centered biomedical-psychological-social model, which promotes the continuous renewal of the concept of enhanced recovery after surgery (ERAS). ERAS adopts a series of perioperative optimization measures with evidence-based medical information. Moreover, ERAS implements a multi-disciplinary collaborative diagnosis and treatment model, such as surgery, anesthesia, nursing, nutrition, rehabilitation, and so on, to reduce the physical and psychological traumatic stress of surgical patients and promote the rapid recovery of patients.^[5]^ Internationally, the ERAS Association has registered in 2010. So far, 15 ERAS guidelines have been issued, including colorectal surgery, heart surgery, hip and knee replacement surgery, lung surgery, and so on.^[6]^ Although there are no guidelines related to ERAS of kidney transplantation, the research on the ERAS project of kidney transplantation has been reported.[^7^,^8^]

When waiting for kidney transplantation, ESRD patients will have functional disorders, such as frailty and decreased cardiopulmonary function, resulting in increased mortality and graft loss rate after kidney transplantation, which affects the clinical application compliance of ERAS regimen and increases the burden of medical insurance.^[9]^ Pre-rehabilitation can optimize the preoperative functional status of patients undergoing elective surgery and then the surgical prognosis.^[10]^ As a type of treatment scheme based on exercise, pre-rehabilitation aims to improve the health status of individuals before the operation to achieve better results after operation.^[11]^ It is an indispensable link in the concept of ERAS. At present, the most commonly used pre-rehabilitation management strategy based on the concept of ERAS is the new pre-rehabilitation management strategy (NEW), which includes nutritional (Nutrition), exercise (Exercise), and coping with anxiety (Worry).^[12]^ It has been confirmed in the intervention trials of cardiothoracic surgery and orthopedic surgery that pre-rehabilitation can significantly improve the short-term effects (hospital stay and postoperative complications) and long-term effects (functional ability and quality of life).^[13]^ In the related studies of abdominal surgery, exercise-based pre-rehabilitation for 3 to 8 weeks can improve the cardiopulmonary function of patients.^[10]^ ESRD patients awaiting kidney transplantation, due to functional decline and muscle atrophy, as well as the desire for kidney transplantation, expect to improve their health to increase the success rate of transplantation, reduce the incidence of postoperative complications, and improve their compliance with pre-rehabilitation, which is very suitable for pre-rehabilitation plans.

In addition to living donation, the timing of kidney transplantation in ESRD patients is unpredictable, and the timing of pre-rehabilitation remains uncertain. The compliance of early implementation will be poor, while patients will not benefit from a too late implementation either. During the period of waiting, ESRD patients need regular hemodialysis or peritoneal dialysis treatment. Regular outpatient exercise increases the time and financial burden of ESRD patients, especially those undergoing peritoneal dialysis. Studies have shown that patients prefer family- and community-based exercise during hemodialysis in hospitals.^[14]^ Therefore, pre-rehabilitation exercise programs conducted at home may be ideal and can reduce the time and financial burden caused by regular visits to rehabilitation clinics. In the study on patients undergoing coronary artery bypass grafting and heart valve surgery, Waite et al have found that preoperative family pre-rehabilitation can reduce the debilitating state of patients, improve the physical function, and shorten the length of hospital stay.^[15]^ This finding shows that family pre-rehabilitation has the potential in improving function and shortening hospitalization days. Williams and others have also actively explored the application of family exercise in patients awaiting liver transplantation.^[16]^ However, the application in ESRD patients awaiting kidney transplantation lacks detailed reports at home and abroad, and more research is necessary to explore its evidence-based medicine.

We hypothesized that personalized family exercise programs for ESRD patients can optimize functional ability, confidence, and motivation during waiting before kidney transplantation, reduce postoperative complications, and optimize transplant results. In the present study, we aim to optimize the family exercise training on the functional ability of ESRD patients undergoing kidney transplantation, and to reduce the adverse effects of frailty, decreased cardiopulmonary function, and psychological dysfunction on the prognosis of kidney transplantation. Before a randomized control trial (RCT) can be conducted, a feasibility study is required to determine whether a larger trial is possible and if so the optimally designed features should be outlined. Therefore, we will conduct a single-center feasibility trial of a novel home-based exercise program in ERSD patients awaiting kidney transplantation. We expect to provide a scientific and valuable reference for the application of family exercise pre-rehabilitation in patients awaiting kidney transplantation.

## Materials and methods

2

The proposed feasibility trial is a single-arm, single-center study of an ERAS-based home exercise pre-rehabilitation for patients listed for kidney transplantation. ESRD patients awaiting kidney transplantation will be selected as subjects to undergo personalized family exercise pre-rehabilitation, including aerobic exercise, functional resistance exercise, and flexibility training. Briefly, a 6-minute walking test (6MWT), 4-meter gait speed, grip strength, and sit-to-stand test will be used as the main outcome indicators. The effect of family exercise pre-rehabilitation on the optimization of body function in ESRD patients undergoing kidney transplantation will be assessed. The days of hospitalization after kidney transplantation, postoperative complications, health survey (the Short Form Health Survey, SF-36), and the Hospital Anxiety and Depression Scale (HADS) will be used as secondary outcome indicators to evaluate the improvement of quality of life, psychological function, and postoperative rehabilitation of patients after kidney transplantation. These indexes will be collected before and after intervention (baseline and before kidney transplantation), before discharge (after kidney transplantation), and 1 month after discharge. In addition, age, sex, race, type of occupation, marital status, education, body mass index (BMI), duration of dialysis, causes of ESRD, and types of renal replacement therapy should be recorded. A study schema is provided in Figure 1.

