#### Primary outcomes

2.6.1

1.Cardiopulmonary function: the cardiopulmonary function will be evaluated by 6MWT, and the maximum distance that the subjects can reach will be measured. The 6MWT is significantly correlated with peak oxygen consumption,^[17]^ which has good reliability and validity and can predict the adverse outcome of ESRD.^[18]^2.Physical fitness: physical fitness will be evaluated by grip strength, 4-meter gait speed and 5 chairs repeated standing tests (5R-STS). Grip strength and lower limb muscle strength are good indicators of systemic muscle strength and reliable predictors of increased risk of hospitalization and death.^[19]^

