### Sample size calculation

2.10

According to existing literature (Manfredini Fabio, Mallamaci Francesca, D’Arrigo Graziella et al. Exercise in Patients on Dialysis: A Multicenter, Randomized Clinical Trial.[J]. J Am Soc Nephrol, 2017, 28: 1259–1268), G-power3.1 software will be used to calculate the sample size. By paired-samples *t* test, the effect size = 0.37, α = 0.05, and power size = 0.80, and the calculated sample size is 47.

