### Statistical analysis

2.11

SPSS24.0 statistical software and Office Excel 2016 will be used to analyze the test data. The quantitative data will be tested by the Kolmogorov–Smirnov test to determine whether they are following a normal distribution. Quantitative data: if the comparison before and after the intervention follows the normal distribution, the paired sample *t* test will be used; if it does not meet the normal distribution, the non-parametric test Wilcoxon symbolic rank test will be used for analysis. The results are expressed as mean ± standard deviation (
$\bar{X}\pm S$
). The postoperative hospitalization days, postoperative complications, postoperative drainage, and extubation are compared with the previous data in the hospital. If the data satisfies normal distribution, an independent sample *t* test will be used; otherwise, the Mann–Whitney *U* test is used for analysis, and the results are all expressed as mean ± standard deviation (
$\bar{X}\pm S$
). The qualitative data will be analyzed by chi-square test (χ^2^ test), and the results are expressed as a percentage (%). The level of significance is *P* < .05.

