This Phase I trial is essential to understand potential recruitment rates, dropout rates, patients who receive transplants or die during the study, and the completion rate of this program to accurately motivate participants for future RCTs.

Collectively, this trial is a practical, single-center, single-arm, exploratory clinical trial. We plan to show that ERAS-based home exercise pre-rehabilitation will reduce the adverse effects of frailty, cardiopulmonary dysfunction, and psychological dysfunction on the prognosis of renal transplantation.

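### Four function tests share primary status at P < .05, the sample size is tied to none of them, and the plan does not say what counts as primary success.

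*Protocol article*

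**What the plan says.** Materials and methods (section 2) states that "a 6-minute walking test (6MWT), 4-meter gait speed, grip strength, and sit-to-stand test will be used as the main outcome indicators"; the Abstract says the same. Primary outcomes (2.6.1) sorts these four tests into two domains. Cardiopulmonary function is measured by the 6MWT, and for the second domain "physical fitness will be evaluated by grip strength, 4-meter gait speed and 5 chairs repeated standing tests (5R-STS"). Neither the domains nor the tests are ranked or combined.

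Sample size calculation (2.10) uses one paired t test: "the effect size = 0.37, α = 0.05, and power size = 0.80, and the calculated sample size is 47". It cites a published trial of exercise in dialysis patients but does not say which of the four tests the 0.37 belongs to, or whether the test is one- or two-sided.

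Statistical analysis (2.11) says that "if the comparison before and after the intervention follows the normal distribution, the paired sample *t* test will be used", with a Wilcoxon test otherwise. It closes with one threshold for everything: "The level of significance is *P* < .05".

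On the purpose of the trial, section 2 says "The proposed feasibility trial is a single-arm, single-center study" and the Discussion says "this trial is a practical, single-center, single-arm, exploratory clinical trial". The next sentence of the Discussion reads "We plan to show that ERAS-based home exercise pre-rehabilitation will reduce the adverse effects of frailty", along with the effects of cardiopulmonary and psychological dysfunction on transplant prognosis.

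**The concern.** A stated power and a stated significance level describe one test. Here four tests have equal claim to be that test. Followed as written, the plan lets whichever of the four crosses .05 be reported as the primary result, and the 5% error rate then no longer describes the claim being made.

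The same gap affects the sample size. An effect size of 0.37 that belongs to no named outcome cannot be checked against the measure on which the conclusion will rest. Nor can it be carried forward cleanly to the randomized trial that this study is meant to prepare.

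The choice of primary outcomes and the basis of the sample size are fixed in this article. A multiplicity procedure written elsewhere could control the error, but it would not restore the stated power, because 2.10 spends the whole 0.05 on one test.

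**Working it through.** **Inputs from the article.** Four primary tests (2, 2.6.1); threshold .05 (2.11); effect size d = 0.37, α = 0.05, power 0.80, n = 47, paired t test (2.10).

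**Assumed.** A common correlation ρ between the four test statistics. The article gives none, so a range is shown.

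**Step 1. Reproduce the 47.** Power of a paired t test is the probability that a noncentral t variable, with n − 1 degrees of freedom and noncentrality d√n, exceeds the critical value (plus the opposite tail if two-sided). At n = 47 the noncentrality is 0.37 × √47 = 2.537.

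- One-sided α = 0.05: critical value 1.679, power 80.3%. With n = 46 power is 79.6%, so the required n is 47. This reproduces.
- Two-sided α = 0.05: critical value 2.013, power 70.0%. The required n is 60. This does not reproduce.

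The article's figure therefore corresponds to a single one-sided test at the full 0.05.

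**Step 2. Familywise error if any one of the four counts.** Under independence, 1 − (1 − 0.05)⁴ = 1 − 0.8145 = 18.5%. For correlated tests, with φ and Φ the standard normal density and distribution function and c = 1.960, the two-sided error is

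1 − ∫ φ(u) · [Φ((c − √ρ·u)/√(1−ρ)) − Φ((−c − √ρ·u)/√(1−ρ))]⁴ du.

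The one-sided version uses c = 1.645 and drops the second Φ term.

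| Assumed ρ | Two-sided | One-sided |
|---|---|---|
| 0 | 18.5% | 18.5% |
| 0.3 | 17.4% | 16.4% |
| 0.5 | 15.6% | 14.4% |
| 0.7 | 13.0% | 12.0% |
| 0.8 | 11.4% | 10.6% |
| 0.9 | 9.4% | 8.8% |

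The two-sided column counts significance in either direction.

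**Step 3. Error if all four must succeed.** The chance that all four are significant cannot exceed the chance that any particular one is. If at least one null hypothesis is true, the error is therefore at most 5%, whatever the correlation.

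**Step 4. Power after adjustment.** Bonferroni gives 0.05/4 = 0.0125 per test. Familywise error under independence is then 1 − 0.9875⁴ = 4.9%. At n = 47 and d = 0.37:

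| | Power at 0.05 | Power at 0.0125 | n for 80% at 0.0125 |
|---|---|---|---|
| One-sided | 80% | 59% | 72 |
| Two-sided | 70% | 48% | 85 |

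The comparison has to be made within a row. Going from 80% to 48% would mix the cost of multiplicity with the separate question of sidedness.

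**The case against.** The strongest objection is the nature of the study. It is a single-arm feasibility trial, calls itself exploratory, and aims to learn recruitment, dropout and completion rates before a randomized trial. No decision to proceed is tied to P < .05 on these tests, and strict familywise control is not an evident requirement for such a study. This stands as a reason to regard the consequence as modest. It does not remove the point: the article makes efficacy measures primary, states a power and a significance level for them, and says it plans to show benefit.

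Second, a multiplicity rule is a detail that an article may leave to a fuller document. That also stands, so the mere absence of an adjustment is not the point here. What remains is what the article itself fixes: four primaries of equal rank and a sample size attached to none. The trial cited in 2.10 may indicate which outcome the 0.37 comes from, but the article does not.

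Third, a reader might infer that the number of tests is four measures times three later assessments, and that the error is far larger. The documents do not support this. Section 2.11 applies the paired test before and after the intervention, and section 2 explains that pair as baseline and before transplantation. That is one contrast per measure. Discharge and 1-month values are collected, but nothing says they are tested for the primary outcomes. Treating repeated measurements in the same patients as independent would also be implausible.

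Fourth, the choice of 6MWT as the single primary is partly preference. It drives only the walking prescription, while the resistance training targets lower-limb and trunk strength, to which the sit-to-stand test is closer. This is accepted: which of the four is named matters less than that one is named.

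**Conclusion.** The point holds as a conditional one. The plan names four co-equal primary tests, applies .05 to each, and sizes the trial on one unadjusted test that it does not identify. If any one significant result is taken as primary success, the two-sided familywise error is about 9–19%, depending on a correlation between 0.9 and 0 that has to be assumed. If all four are required, it is at most 5%.

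A reader might infer that the trial's false-positive rate simply is 13–19%. That goes too far: it presumes the any-one rule, which the article does not state, and correlations no higher than about 0.7, which the article does not give.

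The stated 80% power survives only for a single one-sided test. With Bonferroni over four, power per test is 59% one-sided or 48% two-sided. The change should be made, but in an exploratory feasibility trial it does not undermine the study as a whole.

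**What to change.** - **2.6.1:** name one primary measure, for example 6MWT distance; the sponsor may choose another of the four. State the contrast as baseline to the pre-transplant assessment, which sections 2 and 2.11 already imply.
- **2.10:** say that the effect size of 0.37 refers to that measure and contrast, and state whether the test is one- or two-sided.
- **2.11:** tie the .05 to that one test. Report the other three measures, and all discharge and 1-month values, as secondary estimates with 95% confidence intervals.
- **If all four stay primary:** use Holm's procedure and restate the power in 2.10.

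The cost is wording in three sections. No measurement or visit changes. The downside is that three measures lose the label primary.

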**Figure 1 F1:**
[figure not shown]
Study schema.

### Setting

2.1

The study will be carried out at the Organ Transplant Center of the Second Affiliated Hospital of Hainan Medical University, a 2000-bed Grade 3A general hospital affiliated to Hainan Medical College. This hospital has obtained the national qualification for kidney transplantation in 2010, with annual kidney transplants of about 150.

### Study registration

2.2

The trial protocol is approved by the institutional review board in the Second Affiliated Hospital of Hainan Medical University (LW2020028) and registered on September 2, 2020 at the Chinese Clinical Trial Registry (http://www.chictr.org.cn/showproj.aspx?proj=58570): ChiCTR2000037846.

### Inclusion criteria

2.3

The inclusion criteria will be set as follows:

1.ESRD patients are estimated to undergo kidney transplantation in more than 12 weeks, and the first kidney transplant is on the waiting list of the deceased donor in the Second Affiliated Hospital of Hainan Medical University;2.the age is 18 to 60 years old; and3.patients volunteer and sign the informed consent form.

### Exclusion criteria

2.4

The following patients will be excluded from the study:

1.patients with unstable angina pectoris, new arrhythmia, recent myocardial infarction, or unstable cardiovascular events;2.patients with a recent cerebrovascular accident, or a modified RANKIN score (Modified Rankin Scale, mRS) ≥ 3; and3.those who cannot participate in the exercise due to other serious diseases.

### Study intervention

2.5

All subjects will complete all baseline assessments by trained physiotherapists, who work out and demonstrate personalized exercise prescriptions for each patient according to the results of the functional evaluation, including aerobic exercise, resistance training, and flexibility training. Patients will be trained to correctly use self-perceived exertion (Borg) to monitor exercise intensity, distribute family exercise diaries, and exercise bracelets. In addition to dialysis treatment while waiting for kidney transplantation, the family exercise pre-rehabilitation needs to be completed until the patient returns to the hospital for kidney transplantation, and the functional ability, quality of life, and psychological function of all participants will be then re-evaluated. If the participants stop exercising for 1 week or several weeks due to illness, they can participate intermittently and record the disease and intermittent participation in the case report table, which will be explained in the data analysis.

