### Data collection

2.7

In addition to the data collection involving our primary and secondary outcomes, the information regarding patient demographics and clinical variables, such as age, sex, type of occupation, marital status, education, BMI, dialysis of history, and frequency, causes of ESRD, and type of renal replacement therapy, will be also collected. The above-mentioned features are selectively collected on the admission day (baseline), on the day before operation (second follow-up), on the discharge day (third follow-up), and 4 weeks post-operation (fourth follow-up). The proportion of patients who agree to participate in the trial and the reasons for disagreement will be summarized. Moreover, the number and percentage of participants who complete the complete exercise plan will be also recorded. Scheduled data collection at each time point is presented in Table 4.

**Table 4 T4:** Scheduled events and timeline of the trial.

	Study period					
	Time point	Enrollment	Preoperative	perioperative		Follow up
		12+ weeks before surgery	Before surgery or day of surgery	Discharge	1 month	
Enrollment	**Eligibility screening**	×				
	Informed consent	×				
Interventions	ERAS-based home exercise pre-rehabilitation		×			
Assessments	6MWT	×		×	×	×
	Grip strength	×		×	×	×
	4-meter gait speed	×		×	×	×
	5R-STS	×		×	×	×
	Postoperative condition				×	
	SF-36	×		×		×
	HADS	×		×		×

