### Satisfaction survey

2.9

Before the patient is discharged from the hospital after the kidney transplantation, the satisfaction survey will be completed (Table 5), and the patient is asked to make suggestions on the family exercise program.

**Table 5 T5:** Satisfaction survey.

Satisfaction survey	
Satisfaction with home exercise pre-rehabilitation	□Very dissatisfied □Dissatisfied □Generally □satisfied □ very satisfied.
Does home exercise pre-rehabilitation help you?	□Very dissatisfied □Dissatisfied □Generally □satisfied □ very satisfied.
The degree of difficulty of home exercise pre-rehabilitation	□Very difficult □difficult □Generally □Easy □Very easy

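### Every post-baseline assessment and the satisfaction survey are triggered by transplantation, so the paired change and the satisfaction results describe only those who reach it, after uncontrolled exposure

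*Protocol article*

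**What the plan says.** Section 2.5 (Study intervention) ties the end of the programme to an event: "the family exercise pre-rehabilitation needs to be completed until the patient returns to the hospital for kidney transplantation". It continues that "the functional ability, quality of life, and psychological function of all participants will be then re-evaluated". Section 2.7 (Data collection) places the remaining visits "on the day before operation (second follow-up), on the discharge day (third follow-up), and 4 weeks post-operation (fourth follow-up", and Table 4 uses surgical anchors too. For the survey, section 2.9 says: "Before the patient is discharged from the hospital after the kidney transplantation, the satisfaction survey will be completed".

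On who enters and how long they wait, section 2.3 (Inclusion criteria) requires that "ESRD patients are estimated to undergo kidney transplantation in more than 12 weeks" and that "the first kidney transplant is on the waiting list of the deceased donor". It sets no upper limit on the wait. The Introduction, setting living donation aside, says that "the timing of kidney transplantation in ESRD patients is unpredictable". The Discussion lists dropout, death and the number transplanted among the things the trial must find out.

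The before-after comparison is a paired t test or Wilcoxon signed rank test (section 2.11). It is sized at 47 from an effect size of 0.37, α of 0.05 and power of 0.80 (section 2.10).

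Table 5 asks "Does home exercise pre-rehabilitation help you" and offers five answers running from very dissatisfied to very satisfied.

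**The concern.** A paired test needs two values per person, and under this schedule the second value exists only for someone called in for a transplant. The same holds for the satisfaction form. The plan therefore conditions its primary comparison and its direct measure of satisfaction on an event that it calls unpredictable and that some participants may never reach.

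Three things are at stake. The mean change in those reassessed need not equal the mean change in those enrolled. People who gave up the programme, whose views matter for a feasibility study, never receive the form. And the change is averaged over training periods of very different length, which makes it harder to carry into the design of the randomised trial that this study is meant to prepare.

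**Working it through.** **1. Who can have a second measurement.** Setting the sections side by side:

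- Sections 2.5 and 2.7 and Table 4 give no assessment at a fixed time after baseline. The pre-operative, discharge and final visits all require an operation.
- The sections differ on the last visit (4 weeks after operation in 2.7, 1 month after discharge in the Abstract and section 2). Either way it follows surgery.
- The reference in 2.5 to all participants can therefore cover only those who return for transplantation.
- Section 2.9 places the survey after the transplant.

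**2. Exposure.** The 12 weeks in section 2.3 is an estimate made at entry. An early organ offer gives a shorter period, and nothing limits a longer one.

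**3. Reproducing the sample size.** Inputs from section 2.10: d = 0.37, α = 0.05, power 0.80. For a paired t test with n pairs, power = 1 − F(t_crit; df = n − 1, noncentrality = d√n), where F is the noncentral t distribution function; the two-sided version adds the negligible lower tail.

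- One-sided: the smallest n is 47 (noncentrality 0.37 × √47 = 2.54; power 0.803). This reproduces the plan.
- Two-sided: the smallest n is 60; at n = 47 power is 0.700.

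The stated 47 is thus a number of complete pairs with no allowance for loss. That it matches only a one-sided test is a separate matter. It is noted here so that its effect is not charged to attrition.

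**4. Effect of loss on power.** The document gives no reassessment rate, so the shares below are assumptions. Pairs = 47 × share, rounded. Enrolment to keep 80% power = 47 / share (one-sided) or 60 / share (two-sided), rounded up.

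| Share reassessed | Pairs | Power, one-sided | Power, two-sided | Enrolment for 80%, one-sided / two-sided |
|---|---|---|---|---|
| 100% | 47 | 0.80 | 0.70 | 47 / 60 |
| 90% | 42 | 0.76 | 0.65 | 53 / 67 |
| 80% | 38 | 0.72 | 0.60 | 59 / 75 |
| 70% | 33 | 0.67 | 0.54 | 68 / 86 |
| 50% | 24 | 0.55 | 0.41 | 94 / 120 |

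At 80% reassessed, the loss itself costs about 8 points one-sided (0.80 to 0.72) or about 10 points two-sided (0.70 to 0.60).

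**5. Effect of selection on the mean.** Let f be the share reassessed and D the difference in mean change, in SD units, between those reassessed and those not. The mean for all enrolled is f·m₁ + (1 − f)·m₀, so the mean in those reassessed differs from it by (1 − f)·D. For illustration only:

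- f = 0.9, D = ±0.2: 0.1 × 0.2 = ±0.02 SD
- f = 0.7, D = ±0.5: 0.3 × 0.5 = ±0.15 SD, which is 0.15 / 0.37 = 41% of the planned effect
- f = 0.5, D = ±0.5: 0.5 × 0.5 = ±0.25 SD, or 68%

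The document fixes neither f nor D, nor the sign of D. The identity shows only that the shift can range from trivial to a large part of 0.37.

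**The case against.** The best defence is that function at the time of transplantation is what prehabilitation aims to improve. A later trial on this list would meet the same variable waits, and the study calls itself exploratory. That stands: the pre-transplant assessment should stay, and the observed change is harder to use for planning rather than useless. It is also fair that missing-data analyses are commonly left to an analysis plan that is not shown. Their absence is not the point; the stated visit schedule is.

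Several stronger readings are tempting but not supported:

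- *The change is biased upward.* Death and deterioration could remove poor responders, but others may lack a second value simply because no organ has come. The document does not link waiting to change in function.
- *Acceptability goes unmeasured.* Only the satisfaction form is restricted. Consent proportion, reasons for refusal and completion of the exercise plan (2.7), weekly calls (2.8) and adverse events from screening (2.12) do not depend on surgery.
- *Loss reduces power from 80% to 60%.* That combines attrition with the one-sided basis of the 47.
- *Everyone reassessed has trained for at least 12 weeks.* The entry criterion is a forecast.
- *The second item in Table 5 repeats the first.* The questions differ; the fault is that the answers do not fit the second.

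Extra visits are also not free: the Introduction itself notes that outpatient attendance burdens these patients, especially those on peritoneal dialysis.

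**Conclusion.** The concern holds as a design weakness that should be corrected. Followed as written, the plan yields before-after pairs and satisfaction responses only from participants who reach transplantation, after a training period with no fixed length. As estimates for all enrolled, both may be biased, in a direction and by an amount that the document does not reveal.

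The measurable consequence is that 47 works only if every participant supplies a pair. With 80% reassessed, power is about 72% one-sided or 60% two-sided. That share is assumed. The article gives neither a transplantation rate nor an end date for follow-up, so participants still waiting at the close are an inference from the unpredictable timing and from the Discussion, which treats the number transplanted as unknown. The mismatch in Table 5 is minor but plain on the form.

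**What to change.** (a) **Satisfaction survey.** Give it through the existing weekly call at withdrawal, and at a fixed time such as week 12 to those still waiting. Replace the answers to the second item with a scale from no help to great help. The cost is a form edit and a few minutes within calls already planned.

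(b) **Assessment.** Keep the pre-transplant assessment. Add one reassessment at week 12 for those not yet transplanted, done at a scheduled dialysis or clinic attendance so that no separate journey is needed. The cost is one extra non-invasive assessment per participant. This reduces the gap but cannot close it for those who die or refuse.

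(c) **Reporting.** Whether or not (b) is adopted:

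- Give the numbers transplanted, waiting, withdrawn and dead.
- State that the paired result applies to those reassessed.
- Compare baseline values by reassessment status.
- Add a sensitivity analysis assigning zero change to those not reassessed, labelled as a convention and not an estimate.
- Describe weeks of exposure alongside the change. With about 40 pairs, do not rely on adjustment for exposure.

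These need analysis and text only, and no new data.
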